## Abstract

**Background:**

Anxiety is a problem for many children, particularly because of its negative consequences not only on the wellbeing of the child, but also on society. Adequate prevention and treatment might be the key in tackling this problem. Cognitive behavioural therapy (CBT) has been found effective for treating anxiety disorders. “Coping Cat” is one of the few evidence-based CBT programs designed to treat anxiety symptoms in children. The main aim of this project is to conduct a Randomized Controlled Trial (RCT) to evaluate the effectiveness of a Dutch version of Coping Cat as an indicative group-based prevention program. The second aim is to gain insight into the mechanisms underlying its effectiveness.

**Methods/design:**

Coping Cat will be tested in Dutch primary school children grades five through eight (ages 7 to 13) with elevated levels of anxiety. This RCT has two conditions: 130 children will be randomly assigned to the experimental (N=65, Coping Cat) and control groups (N=65, no program). All children and their mothers will be asked to complete baseline, post intervention, and 3-month follow-up assessments. In addition, children in both the experimental and control group will be asked to complete 12 weekly questionnaires matched to the treatment sessions. Main outcome measure will be the child’s anxiety symptoms level (SCAS). Four potential mediators will be examined, namely active coping, positive cognitive restructuring, self efficacy and cognitions about ones coping ability (from now on coping cognitions).

**Discussion:**

It is hypothesized that children in the experimental condition will experience reduced levels of anxiety in comparison with the control group. Further, active coping, positive cognitive restructuring, and coping cognitions are expected to mediate program effectiveness. If Coping Cat proves effective as a prevention program and working mechanisms can be found, this group-based approach might lead to the development of a cost-effective program suitable for prevention purposes that would be easily implemented on a large scale.

**Trial Registration:**

Nederlands Trial Register
NTR3818.

## Background

Anxiety disorders are known as one of the most common psychiatric disorders in children. Prevalence rates of anxiety disorders in children vary widely from 5% to 23% due to differences in measurements, target groups and recognition of the problems
[1-3]. Kessler and colleagues
[4] showed that about 75% of anxiety disorders start between 11 years and 21 years of age. Anxiety disorders are also known for their wide range of detrimental consequences. Social competencies, self-esteem, and academic achievement are negatively associated with anxiety disorders
[3]. Anxiety in childhood has been associated with greater risk for; more severe anxiety and substance abuse in adulthood
[5]. Further, about 30% of the clinically anxious youth have comorbid depression disorder
[6]. Altogether, anxiety symptoms in children should be perceived as a serious problem.

The vast majority of children and adolescents with high levels of anxiety do not seek treatment
[7]. Partly because of the difficult distinction between normal anxiety in children and symptoms of an anxiety disorder, plus the different manifestation of anxiety in children (more externalizing than internalizing). Underreporting, as well as underdiagnosis, results in a substantial number of children and adolescents with unnoticed and untreated subclinical and clinical anxiety. Indicative prevention might be the key for detecting and treating these symptoms early and preventing future problems.

Meta-analytic review
[3] showed that anxiety prevention works best when it’s on indication (only children with elevated anxiety levels participate) focused primarily on anxiety problems and given by well-trained therapists. Furthermore, children under the age of 11 seem to benefit more from prevention programs compared to older children. This pleads for testing a theory-based anxiety program in young children with elevated levels of anxiety. Cognitive behavioural therapy (CBT) is the most effective treatment for anxiety disorders
[8,9]. “Coping Cat” is one of the few effective CBT programs for anxiety symptoms in children. This program includes both cognitive techniques (cognitive restructuring and handling physiological responses to anxiety) as behavioural components (relaxation training, exposure). The focus is on exposure, which begins early in the program. Coping Cat has been proved effective in the US
[5,10] as well in several other countries, including the Netherlands
[11,12]. Although most studies focused on individual treatment, a few studies evaluated a group intervention, which has been found to be just as effective as the individual intervention
[13,14]. Because of its effectiveness in clinical samples, therapeutic basis and substantial exposure components, we will test the effectiveness of an indicated group-prevention version of Coping Cat.

Although Coping Cat is effective in decreasing the levels of anxiety and fears, it is still largely unknown what components of this program are essential working elements. To obtain insights into the program’s working mechanisms and eventually optimize the treatment and prevention of anxiety, it is essential to study mediators of change
[15]. Beck’s cognitive model assumes that anxious individuals process stimuli in a biased way, resulting in several cognitive errors
[16]. Exaggerated perception of danger and an underestimation of one’s ability to cope with these threats are associated with these biased interpretations
[17]. An important mediator between experiencing a stressful life event and emotional well-being is coping. Coping is a broad term that includes cognitive, behavioural, and physiological processes and indicates how one responds to stressful situations
[18]. Based on several studies, coping skills and self-efficacy are linked to reduction of anxiety symptoms
[19]. Maric et al.
[20] indicated that one of the strongest predictors of anxiety is the underestimation of the ability to cope. This suggests that cognitions about one’s coping abilities play a mediating role in anxiety treatment. Kendall found some evidence for this claim
[21]. Coping is a comprehensive concept, which can be measured using more general as well as more specific strategies. A meta-analysis
[22] showed that coping plays a mediating role in treatment gains, regardless of whether it is measured as a general (e.g., self-efficacy, coping strategies) or a specific strategy (coping cognitions). We aim to test whether active coping, positive cognitive restructuring, self-efficacy, and cognitions about coping ability mediate the effect of CBT treatment on anxiety in children.

### Aim and hypothesis

The main aim of this project is to conduct a Randomized Controlled Trial (RCT) to evaluate the effectiveness of a CBT based program called Coping Cat on the anxiety levels of Dutch primary school children. Therefore, Coping Cat will be revised and used as an indicative prevention group-based program. In this RCT, we will assign children to an experimental and a control group to test whether children who received Coping Cat as an indicated-group prevention program will have lower levels of anxiety at follow-up measurements. The second aim is to determine whether active coping, positive cognitive restructuring, self efficacy and coping cognitions operate as mediators. More specifically, we expect that a) anxiety levels of children in the prevention program will decrease significantly more over time compared to anxiety levels of children in the control group. b) Children who will follow the program will have significantly enhanced coping skills compared to the control group.

## Methods/design

### Study design

Coping Cat will be adjusted and tested as an indicated CBT-based prevention program in Dutch primary school children, grades five through eight, with elevated levels of anxiety. This study is set up as a RCT with two conditions, with 130 children being randomly divided into the experimental (N=65) and control group (N=65). The experimental group will receive the adapted 12-session Coping Cat program. The control group will not receive a program. They will be offered the possibility to follow the program at the end of the study. Participating children and their mothers will complete baseline, post intervention, and a 3-month follow-up assessments (see Figure 
1). In addition, children in both experimental and control group will be asked to complete questionnaires weekly, just before every program session. All mothers who will complete all questionnaires will receive about 50 Euros for their participation. Children will receive few small for their participation.

**Figure 1 F1:**
[figure not shown]
Study design.

### Participants

#### Recruitment

Children will be recruited from a sample of primary schools in the Nijmegen-region in the Netherlands. Schools will be asked to participate and distribute a letter to all children from grades five till eight, in which we will inform children and parents about this study. Parents who do not want their child to participate in the screening can return an enclosed objection form. After screening, all parents will be informed about their child’s anxiety level, as revealed by the screening questionnaire. Parents whose children will have significantly increased levels of anxiety will be contacted by telephone. This will done to assure that they understand the implications and limitations of these results. In contrast to the passive consent procedure regarding the screening, active consent will be obtained for children’s participation in the intervention and control group. By signing and returning an attached consent form, parents will provide permission for their child(ren) to participate in one of the groups. This study received approval from the Faculty Ethics Committee.

#### Eligibility criteria

To be included in the screening, children will have to be in grades 5–8 in one of the participating Dutch elementary schools. Moreover, the children as well as their parents will have to speak and read Dutch to be able to complete the questionnaires and participate in therapy sessions. To participate in the RCT, children will have to report their levels of anxiety. This will be measured using an anxiety questionnaire (Spence Children’s Anxiety Scale)
[23]. All children who will score above a 1 SD cut off score will be included. In addition, children who will score above the cut off score on the obsessive-compulsive disorder scale only will not be able to participate in the study. Children with OCD are known to respond better to specific CBT treatment
[24]. Parents of children who will score high on suicidal ideation (1 item, Child Depression Inventory)
[25] will be contacted by telephone by an experienced therapist to make sure this information is communicated carefully. Subsequently, it will be decided whether the child can participate in the study or whether referral to mental health care is needed. Children who followed CBT during the preceding year or will be following a treatment with a CBT basis will not be able to participate in the study. When the child already has knowledge on specific cognitive techniques, this will interfere with determining the underlying mechanisms. Children with diagnosed comorbidity, such as ADHD, ODD, and the like, will be eligible.

#### Randomization

Randomization will be applied within schools, with an equal number of experimental and control groups within one school. Children will be assigned to either the treatment or the control condition. Participants will be stratified by age (young: 7–9 years. & old: 10–12 years) and number (equally distributed over both conditions).

#### Sample size calculation

Based on the outcomes of Coping Cat effect studies abroad and in the Netherlands, a high effect size is expected
[11,13]. However, all these children were residing in a child welfare institution and diagnosed with an anxiety disorder. The anxiety problems are thus expected to be more severe in these children compared to the participants in the current study. Therefore, the effect of the intervention in this study is expected to be smaller. Research on indicated anxiety prevention
[3] has shown that effect sizes around .32 can be expected. To be on the safe side, we estimated a medium effect of F^2^ .15 at three months follow-up, and further increased the sample to account for clustering of the data, which lead to 65 participants per condition. About 30% of the children are expected to have elevated levels of anxiety, with an expected response rate of 60% of these children with elevated levels of anxiety participating, about 700 children should be approached.

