### Program intervention

A Dutch Coping Cat group therapy program will be used as an indicated prevention. We adjusted a Dutch version of the individual orientated program
[26] according to the content of the American group therapy version of Coping Cat
[27]. The main changes concern the increased duration of the program (from 18 to 12 sessions), increased number of group elements, and decreased contact time (from 2 hours to 1 hour). Moreover, the exposure exercises will start earlier in the program (session 4 instead of session 8).

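### The planning effect of f² = .15 is presented as cautious, but it exceeds the expected effect of .32 whether that figure is read as d, Cohen's f or r

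*Protocol article*

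**What the plan says.** The Sample size calculation section argues in steps. Earlier Coping Cat studies showed a high effect, but in children with diagnosed disorders, and so: "Therefore, the effect of the intervention in this study is expected to be smaller". For indicated anxiety prevention, the cited research "has shown that effect sizes around .32 can be expected"; the scale of .32 is not named. The planning value follows: "To be on the safe side, we estimated a medium effect of F^2^ .15 at three months follow-up". The authors then "further increased the sample to account for clustering of the data", "which lead to 65 participants per condition". Study design confirms equal allocation: "130 children being randomly divided into the experimental (N=65) and control group (N=65".

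Statistical analysis makes anxiety at the 3-month follow-up the main outcome. It is tested by regression, and effect sizes and confidence intervals will be reported.

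**The concern.** The paragraph reads as a step down from .32 to a more cautious .15. The two numbers can only be ordered once they are on the same scale. Cohen's f² is a squared quantity, so a numerically small f² can stand for a large difference between groups. If the planned effect is really the larger one, the only justification given for the sample size claims a safety margin that is not there. Readers would then overrate the trial's sensitivity to an effect of the size the authors themselves expect, and could take a non-significant result as stronger evidence against prevention than it is.

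**Working it through.** **Inputs from the protocol article.** Planning effect f² = .15; expected effect .32, scale not stated; 65 per arm, allocated 1:1; therapy groups of 7 to 9 children (Intervention condition).

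**Assumed, because the article does not give them.** Two-sided 5% test, no dropout, range of intraclass correlations (ICC), range of baseline correlations.

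**1. The plan's own figure.** A regression test of one predictor with f² = .15 needs 55 children in total for 80% power, 73 for 90% and 89 for 95%. Reaching 130 then implies an overall inflation of 130/55 = 2.36, 130/73 = 1.78 or 130/89 = 1.46. Power, number of predictors and ICC are not stated, so 65 per arm can be neither confirmed nor refuted. The finding does not rest on that.

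**2. Planning effect as a standardised difference.** For two equal groups without covariates, f² = d²/4, so d = 2√.15 = 0.775.

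**3. Expected effect on the same scale, and power at 65 per arm** (noncentral t, unadjusted, no clustering):

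| Reading of .32 | f² | d | Power |
|---|---|---|---|
| d | .32²/4 = .026 | 0.32 | 44% |
| Cohen's f | .32² = .102 | 2 × .32 = 0.64 | 95% |
| r | .32²/(1 − .32²) = .114 | 2 × .32/√(1 − .32²) = 0.676 | 97% |
| f² | .32 | 2√.32 = 1.13 | above 99% |
| *Planning value* | *.15* | *0.775* | *99%* |

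The first three readings all lie below f² = .15. Only the fourth would make .15 the cautious choice.

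**4. Therapy-group clustering in the experimental arm.** Assume eight groups, so a mean size of 65/8 = 8.125, and ICC .05, .10 or .15. The experimental-arm design effect is 1 + 7.125 × ICC. Averaged with 1 for the controls, this gives 1.18, 1.36 and 1.53.
- If .32 is d: power 39%, 34% and 31%.
- If .32 is f or r: from about 94% (r, ICC .05) down to about 83% (f, ICC .15).

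**5. Baseline adjustment, if .32 is d, no clustering.** The effective difference is .32/√(1 − ρ²) for baseline correlation ρ. Power is about 55% at ρ = 0.5, 62% at 0.6, 72% at 0.7 and 85% to 86% at 0.8 (noncentral t and normal approximation). For d = .32 to amount to f² = .15 would take ρ = √(1 − (.32/.775)²), about .91.

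**6. Detectable d at 80% power with 65 per arm.**
- Unadjusted, no clustering: 0.495, about 0.50.
- Unadjusted, ICC .05 to .15: 0.495 × √1.18 to 0.495 × √1.53, about 0.54 to 0.61.
- Baseline adjustment at ρ = 0.5 to 0.6, no clustering: 0.495 × √.75 to 0.495 × √.64, about 0.43 to 0.40.

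**The case against.** The strongest reply is that the scale of .32 lies in a cited review that is not at hand. The power consequence depends on it: 44% under one reading, 95% to 97% under two others. That stands. A reader might infer that the trial has only 44% power and is more likely to miss the expected effect than to find it. The article does not support that without conditions. It holds only if .32 is d and the analysis is unadjusted.

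Second, the planned regression may well adjust for baseline: the article tests for a stronger decrease and collects the anxiety scale at baseline. This also stands as a limit on the 44% figure. It does not restore the claim of caution, because only a baseline correlation near .91 would bring d = .32 up to f² = .15.

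Third, .32 could itself be an f². The text does not exclude this, since it gives no number for the clinical effect. But d = 1.13 is implausible as the expected effect in a passage that expects less than in clinical samples.

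Fourth, the sample was increased for clustering. The amount is not given, and the increase was applied to a base built on the larger effect, so it does not make the planning effect cautious.

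A reader might also infer from the reduced sessions and the "decreased contact time (from 2 hours to 1 hour" that the expected effect should be lower still. That does not follow. The sentence compares this programme with another version of Coping Cat, not with the prevention programmes behind .32, and it is garbled: it calls a change from 18 to 12 sessions an increase in duration.

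**Conclusion.** The point holds as a mis-scaled justification. Whether .32 is d, Cohen's f or r, the planning effect is larger than the expected one: f² of .15 against .026, .102 or .114. The claim of caution is therefore the wrong way round.

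The size of the consequence is conditional. If .32 is d, power with 65 per arm runs from 31% (unadjusted, ICC .15) through 44% (unadjusted, no clustering) to about 86% (baseline correlation 0.8, no clustering). If it is f or r, power stays at about 83% or more over the same ICC range. All figures assume a two-sided 5% test and no dropout; the ICCs and baseline correlations are assumptions, not values from the article. The figure of 65 per arm is not shown to be wrong as a calculation.

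**What to change.** Keep 130 children and rewrite the sample size paragraph:
- Name the scale of .32, and give the expected and planned effects on one scale (f² = .15 is d = 0.775).
- Remove the claim of caution.
- State the detectable effect at 80% power with its assumptions: d of about 0.50 unadjusted without clustering; about 0.54 to 0.61 with ICC .05 to .15; about 0.40 to 0.43 with baseline adjustment at correlations of 0.6 to 0.5 and no clustering.
- Give power at the expected effect as a conditional figure, with the reading of .32, the covariates and the ICC it assumes.
- Say that a non-significant result will be interpreted through the confidence interval, which Statistical analysis already plans to report.

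The cost is one reworded paragraph and a less favourable stated sensitivity. Recruitment, design and analysis do not change.

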### Program intervention

A Dutch Coping Cat group therapy program will be used as an indicated prevention. We adjusted a Dutch version of the individual orientated program
[26] according to the content of the American group therapy version of Coping Cat
[27]. The main changes concern the increased duration of the program (from 18 to 12 sessions), increased number of group elements, and decreased contact time (from 2 hours to 1 hour). Moreover, the exposure exercises will start earlier in the program (session 4 instead of session 8).

#### Intervention condition

Children randomly selected to the intervention condition will receive a 12-session group program, each session lasting 1 hour. The sessions will take place every week, except for holidays. Groups consist of 7 to 9 children. The program will take place in schools after regular school hours. The program will start by using exercises enhancing group cohesion and safety. These exercises will continue throughout the program. In session 2 and 3, psycho-education about anxiety will be given and anxious feelings, both physical and emotional, will be addressed. Moreover, a relaxation exercise will be introduced. Children will be motivated to keep rehearsing relaxation every day during several weeks. The next step (session 4) will be to recognize thoughts and stimulate positive thinking. Meanwhile, exposure will be introduced beginning with session 4. Children will practice different anxiety provoking situations as homework at home, thus in low anxiety situation. In group therapy, children learn to make a plan when entering anxious situations (session 5). Beginning with session 6, children will experience anxious situation during therapy. They will start easy, being exposed to low-level anxiety situations as a group and slowly experiencing high-level anxiety situations that they will face alone. Meanwhile, children will repeat the techniques they acquired. Session 12 will end with an evaluation and little party to celebrate the children’s results. Parents will receive written information three times during the program, with specifics about the progress of their child and general information about the program.

#### Trainers

Trainers (n=5) are child psychologists with ample experience in youth mental health care and knowledge of CBT. All trainers will participate in two-day training. In this training, the protocol will be explained and trainers will complete exercises and role-plays. Therapists will follow 2-h supervision sessions three times over the course of the program. A MA student in clinical child psychology will assist each therapist.

#### Control condition

Children in the control group will be asked to complete questionnaires weekly while children in the program will be completing these questionnaires. Children will be administered the Coping Cat directly after the 3-month follow-up assessment.

### Data collection

Children will receive all questionnaires on paper and complete them at school, after school hours, in the presence of one of the researchers or trainers. This context is chosen deliberately to exclude any influence of parents. Mothers will complete the pre-, post-, and follow up measurement online. For this purpose, they will receive separate personal login codes that will give them access to their own questionnaire on a secured webpage. Mothers who prefer a paper questionnaire will be provided with a paper and pen version. Interference of the researcher will be diminished as much as possible by presenting the questionnaires digitally. Children and mothers are expected to complete the pre-, post-, and follow up assessments within 45 minutes. The weekly measurements will take about 10 minutes to fill out. Non-responding mothers and absent children will be contacted by phone and motivated to complete the questionnaire on paper or directly by phone. An overview of all measures at each time point is provided in Table 
1.

**Table 1 T1:** Overview of measures

**Measure**	**Screening**	**Baseline**		**Weakly**		**Post treatment**		**3 month follow up**	
	**Child**	**Child**	**Mother**	**Child**	**Therapist**	**Child**	**Mother**	**Child**	**Mother**
Spence Children's Anxiety Scale (SCAS)	X	X	X			X	X	X	X
Multidimensional Anxiety Scale for Children (MASC- 10)		X		X		X		X	
Suicidal item Child Depression Inventory (CDI)		X				X		X	
Coping Strategies For Children^1^ (CSLK)		X		X		X		X	
The Self-Efficacy Questionnaire for Children^2^ (SEQ-C)		X		X		X		X	
Coping Questionnaire Child (CQ-C)		X		X		X		X	
Therapeutic Alliance Scale for Children (TASC)				Session 1/6/12	X				
Demographic characteristics		X	X						
5 most anxious situations (for treatment purposes)		X							

^1^ Subscales used: Active coping & Positive cognitive restructuring.

^2^ Subscale used: Emotional self efficacy.

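### Trainers who deliver Coping Cat may be present while children fill in the self-reported outcomes, which could add reporting bias that differs between arms

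*Protocol article*

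**What the plan says.** All quotations are from the protocol article.

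- **Who is in the room.** Under Data collection, children fill in paper questionnaires at school once lessons are over, "in the presence of one of the researchers or trainers". The sentence covers all child questionnaires. It does not say which adult attends which arm or which time point.
- **Why this setting.** The reason given concerns parents only: "This context is chosen deliberately to exclude any influence of parents". A second safeguard follows the description of the mothers' online forms: "Interference of the researcher will be diminished as much as possible by presenting the questionnaires digitally".
- **Who the trainers are.** "Trainers (n=5) are child psychologists with ample experience in youth mental health care and knowledge of CBT". The Trainers section also describes their instruction in the program and their supervision while it runs, and calls them therapists as well.
- **Weekly forms.** Under Study design, "children in both experimental and control group will be asked to complete questionnaires weekly, just before every program session". Under Control condition: "Children in the control group will be asked to complete questionnaires weekly while children in the program will be completing these questionnaires".
- **What is measured.** Outcome names the SCAS as primary, and Statistical analysis fixes the 3-month child value as the main outcome. In Table 1 the child SCAS is taken at screening, baseline, post-treatment and 3 months, and not weekly. The weekly child forms are the MASC-10, CSLK, SEQ-C and CQ-C, with the child TASC at sessions 1, 6 and 12. Mothers complete the SCAS at baseline, post-treatment and 3 months, and none of the mediator scales.
- **Control arm.** Control children are given the program only after the 3-month assessment.

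**The concern.** The protocol accepts that an adult nearby can influence a child's answers: it keeps parents away and tries to limit the researcher's influence. The trainer is the adult with the most direct interest in seeing improvement, and no safeguard applies to the trainer.

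The children are 7 to 13 years old, know whether they received the program, and report both the primary outcome and all candidate mediators themselves. After 12 sessions, an experimental child may answer differently in front of a trainer, while a control child has no such relationship. If the shift is towards less reported anxiety and more reported coping, the main effect and the mediation path are inflated together, because outcome and mediators share a reporter and a setting. The alliance scale has a related problem that is not a comparison between arms: a child may rate a relationship with the rated person in the room.

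Once the data are collected, no analysis of the child reports can separate such a shift from a program effect.

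**Working it through.** The protocol gives no figure for this bias, so there is nothing to reproduce. The check is mainly a reading of the sections against one another.

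**1. Does the permission reach the primary outcome?** Yes. The Data collection sentence has no exception, and Table 1 lists the child SCAS at 3 months. The wording about completion just before each session does not reach it, because the SCAS is not a weekly form. That wording bears on the mediators and the weekly MASC-10, when the trainer is likely to be on hand.

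**2. Does a stated safeguard cover it?** No. The measure against parents does not concern trainers. Digital presentation cannot protect forms that children fill in on paper. Strengths and limitations mentions contamination between arms but not this.

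**3. Can it differ between arms, and when?**

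| Time point | Experimental children treated by a trainer? | Control children? | Can this mechanism differ by arm? |
|---|---|---|---|
| Baseline | No | No | No |
| Weekly forms | Yes, once sessions begin | No | Yes |
| Post-treatment | Yes | No | Yes |
| 3 months (primary) | Yes, sessions ended | No | Yes, perhaps more weakly |

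**4. Is there an independent check?** In part. The mother SCAS is normally completed online, away from the trainer. Mothers are not described as blinded, and they do not rate the mediators.

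**5. What would a shift do? (illustration only)**

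Assumptions, none from the protocol: a one-arm shift of b SD, no true effect, two-sided alpha 0.05, normal approximation, no clustering or covariate adjustment. From the protocol: 65 per arm.

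SE = √(2/65) = 0.175 SD.

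Rejection probability = Φ(b/SE − 1.96) + Φ(−b/SE − 1.96).

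| Assumed b (SD) | b/SE | Rejection probability |
|---|---|---|
| 0 | 0 | 5% |
| 0.1 | 0.57 | 9% |
| 0.2 | 1.14 | 21% |
| 0.3 | 1.71 | 40% |

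The formula is the same for a shift against the program, except that the false finding would then be of harm.

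Sample size calculation gives two effects against which to set a shift. It cites about .32 from the prevention literature without stating the metric. If that is an SD difference, 0.1/0.32 = 31% and 0.2/0.32 = 63%. It plans on f² = .15, which for two equal groups is d = 2√0.15 = 0.775. Then 0.1/0.775 = 13% and 0.2/0.775 = 26%. So the relative size depends on the assumed shift and on the yardstick, and the document fixes neither.

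**The case against.** The strongest reply is that the text permits a trainer to be present but does not say that a child's own trainer will be. There are five trainers, researchers are named as the alternative, and the weekly forms are completed by both arms at the same time. If that is one sitting, one adult supervises both arms. This stands as far as it goes: the presence of a trainer in the experimental arm alone is not stated. It does not remove the asymmetry, because the same trainer in front of both arms has still treated only one of them.

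The direction is also open. A trusted trainer, in a program that teaches children to recognise anxious feelings, could draw out fuller disclosure and higher reported anxiety. This stands. A shift in favour of the program is plausible but not shown.

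The primary assessment comes after the sessions have ended, which may weaken the mechanism there. A researcher in the room would not remove demand effects either, since children know what they received. Both points limit what the fix can achieve; neither is a reason to leave the most interested adult in the room.

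Finally, a condensed article commonly leaves details of supervision and form handling to the full protocol. That would answer a complaint about silence. Here the article states a permission, and the permission is what is at issue.

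**Conclusion.** The point holds as a risk of differential reporting bias on the primary outcome and the mediators, arising from a stated permission with no safeguard against it. It rests on two readings: that the trainers are the people who deliver the program, and that the Data collection sentence applies to every child assessment, as it is worded.

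A reader might infer more: that the arrangement does bias one arm in favour of Coping Cat, by something like a third to two thirds of the expected effect. The document does not support that. It does not say which adult sits with which arm, it does not settle the sign, and the mechanism cannot act at baseline. The 31–63% range needs both an assumed shift of 0.1–0.2 SD and the reading of .32 as an SD difference. The error rates shown above likewise only restate assumed shifts.

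The mother SCAS lowers the risk for the conclusion on anxiety but not for the mediators. The change is worth making because it is cheap and because the bias cannot be removed afterwards.

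**What to change.** 1. **Post-treatment and 3 months.** Remove trainers from those who may be present at the child assessments. Have one of the researchers already in the plan, who does not deliver the program, supervise both arms in the same way and, where possible, in the same sitting. Baseline need not change on this ground.
2. **Weekly forms and the child alliance scale.** The trainer may be on hand for these, so have children hand in folded or sealed forms that the trainer does not read.
3. **Supporting analysis.** Report the mother SCAS alongside the child result, noting that mothers are not described as blinded.

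**Cost.** Less flexibility on the day, researcher time at two assessment points, and a small added step in handling the forms. The article gives no number of researchers or schools, so whether existing staff suffice cannot be confirmed from it. Demand effects from unblinded children remain in part and belong among the stated limitations.
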